### Strategies to improve adherence to interventions {11c}

The number of active sessions attended (i.e. sessions involving active avatar dialogue) by the participant will be measured to assess treatment adherence. Fidelity to the clinical manual will be assessed by the therapist completing a session-by-session checklist of specified components (these will also be used during training and ongoing supervision- see above). Each session will be audio recorded with consent. After completion of training, therapist competence will be assessed by an expert in AVATAR therapy for general/clinical and AVATAR-specific skills using ratings adapted from the first AVATAR therapy trial and allowing for differing skill requirements for each level of therapy. Each trial therapist will be rated for competence based on the review of early, mid and late session therapy delivery for at least one completed intervention. Ratings will be conducted for two cases for therapists who deliver completed therapy with more than five participants.

### Relevant concomitant care permitted or prohibited during the trial {11d}

Participation will not alter clinical treatment decisions about medication and additional psychological and psychosocial interventions which remain the responsibility of the clinical team. The antipsychotic medication prescribed to participants in the study and psychological and psychosocial interventions provided will be recorded.

### Provisions for post-trial care {30}

There is no provision for post-trial care in the study and participants will remain under the care of their usual mental health services. The trial is covered by the Sponsor’s (King’s College London) indemnity insurance.

### Outcomes {12}

The primary outcome for the study is reduction at end of treatment (16 weeks) and follow up (28 weeks) in the distress associated with voices, as measured by the distress dimension of the Psychotic Symptoms Rating Scale (PSYRATS-AH) [29, 30].

We note the recent CONSORT-SPI guidance which recommends minimising the distinction between primary and secondary outcomes, therefore all outcomes will be reported at the end of the trial [31].

All measures are detailed in Table 1.

**Table 1 Tab1:** AVATAR2 measures

	Measure	Time-point*
Distress, Frequency and Severity of Voices Outcome Measures	Psychotic Symptom Rating Scales – Auditory Hallucinations – a dimensional measure of hallucinations [29]. Includes Distress dimension (primary outcome), Total score (secondary outcome), and Frequency dimension (secondary outcome) [30]. Hallucinations Remission Score	Screening, 1, 2, 3
Other Voices Outcome Measures	Beliefs about Voices Revised (BAVQ-R) [32]. Voices acceptance and action scale (VAAS) [33]. First item (power) from the Voice Power Differential Scale [34].	1, 2, 3
Experience Sampling Methodology	AVATAR2 ESM Questionnaire [35].	1,2,3
	AVATAR2 ESM Debrief Questionnaire [36].	1,2,3
Other Secondary Outcome Measures	Mood: Beck Depression Inventory-II [37].	1, 2, 3
	Anxiety: Depression Anxiety and Stress Scales (DASS-21) [38].	1,2,3
	Quality of Life: Warwick-Edinburgh Mental Well-being Scale [39].	1, 2, 3
	Delusions: Psychotic Symptoms Rating Scale (PSYRATS-DEL) [29].	1, 2, 3
	Service User Led Outcome Measure: Choice of Outcome in CBT for Psychosis (CHOICE) Short Form [40].	1,2,3
	Trauma related symptoms – International Trauma Questionnaire (ITQ) [41].	1, 2
Health Economic Outcome Measures	Service use and costs: costs of the intervention (based on staff time, overheads and equipment) and the costs of other key health and social care services calculated using the [42].	1, 2, 3
	EQ-5D-5L [43] to measure QALYs	1, 2, 3
Baseline Clinical Characteristics	Voice Characterisation Checklist: Assesses the complexity in characterisation of the dominant voice. Rated as more vs. less highly characterised based on presence/absence of ascribed identity (e.g. known, name), physical characteristics (e.g. age, gender, accent) and psychosocial characteristics (e.g. intentions, thoughts, relationships)-see [21]. Including two items from the Voice Phenomenology Interview [44].	1
	Fearful Attachment Style Item from Relationships Questionnaire [45].	1
	Patient perceived trauma-voice links - Trauma Voice Associations Questionnaire (TVAQ)	1
	Trauma history - Mini-Trauma And Life Events (TALE) checklist [46].	1
	Clinical Assessment Interview for Negative Symptoms (CAINS) [47].	1
	Identification of positive symptoms – Initial items from the Schedules for Clinical Assessment in Neuropsychiatry (SCAN) 2.1 [48].	1
	Detailed assessment of positive symptoms - Scale for the Assessment of Positive Symptoms [49].	1
Covid-19 Impact	Covid-19 Context Questionnaire to assess individual circumstances during pandemic and change in voice experiences.	1, 2, 3

^a^1 = baseline, 2 = 16 weeks post-randomisation, 3 = 28 weeks post-randomisation

### Participant timeline {13}

Figure 1 shows the participant timeline.

**Fig. 1 Fig1:**
[figure not shown]
Participant Time Schedule

### Sample size {14}

We will recruit 345 people in total for the study (approximately 87 per site and 115 per arm). The effect size in the sample size calculation is based on the findings of the previous AVATAR therapy trial [16] which reported clinically meaningful reduction in PSYRATS-AH distress dimension post-treatment of 4.8 points, with an effect size of approximately *d* = 0.8. This has been conservatively reduced for the current trial, to take into consideration the increase in the number of centres, the comparison at both post-treatment and follow-up and a more pragmatic trial design. We are accounting for two formal comparisons (hypothesis 1 and 2).

The study is powered for an overall treatment effect at a 5% alpha level, accounting for 2 multiple comparisons in which the tests are correlated (at *r* = 0.5), giving an alpha level for each test of 0.035. Accordingly, a sample size of 92 per group or 276 in total will have 90% power to detect a minimum clinically significant difference (effect size) of 0.5 standard deviations. We will recruit 345 participants in total at baseline, allowing for an attrition of 20%.

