## Statistical methods

### Statistical methods for primary and secondary outcomes {20a}

We will report all participant flow in the study in accordance with the CONSORT principles, with the 2018 extension for reporting social and psychological intervention trials ((CONSORT SPI) [31]). Descriptive statistics will be used to summarise assessments of recruitment, drop-out and completeness of therapy.

The primary outcome of voice-related distress as measured by PSYRATS-AH distress dimension score will be analysed using a mixed effects model including data from all time points. Fixed effects will be site, characterisation, baseline assessment for the outcome under investigation, random allocation, time and time*random allocation interactions. Participant and therapist will be included as random intercepts, with the participants in the TAU arm considered as being in individual clusters of size 1. Marginal treatment effects for each pairwise comparison will be estimated for outcomes at each time point and reported separately as mean adjusted differences in scores between the respective randomised groups with 96.5% confidence intervals and two-sided *p* values (to account for correlated multiple comparisons). For continuous secondary outcomes, the same approach will be followed, and for binary secondary outcomes, logistic mixed models will be used.

The random effect structure will account for repeated measures and clustering due to the partially nested design and allow estimates of separate ICCs in both randomised arms.

Cohen’s d effect sizes at 16 and 28 weeks will be calculated as the adjusted mean difference divided by the sample standard deviation of the outcome at baseline and displayed in a forest plot.

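### A per-test alpha of 0.035 does not hold the stated 5% overall level: at the plan's own correlation of 0.5 the family-wise error is 6.4%, and the 96.5% intervals are too narrow

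*Protocol article*

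**What the plan says.** Sample size {14} sets the error rate: "The study is powered for an overall treatment effect at a 5% alpha level". It names the family: "We are accounting for two formal comparisons (hypothesis 1 and 2"), that is, each form of therapy against TAU. The adjustment is described as "accounting for 2 multiple comparisons in which the tests are correlated (at *r* = 0.5"), and the result as "giving an alpha level for each test of 0.035". No method is named for getting from 5% to 0.035.

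The sample size rests on that level: "a sample size of 92 per group or 276 in total will have 90% power". The effect that the trial is sized for is called a "minimum clinically significant difference (effect size) of 0.5 standard deviations". The total is then raised to 345 for 20% attrition.

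The statistical methods section {20a} applies the same level to the analysis. Adjusted mean differences are to be reported with "96.5% confidence intervals and two-sided *p* values (to account for correlated multiple comparisons"). So 0.035 is both the planning figure and the decision rule for the primary outcome.

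**The concern.** The article fixes three quantities: the overall level (5%), the correlation between the two tests (0.5) and the per-test level (0.035). For two two-sided tests, any two of these determine the third, so the set can be checked without outside information.

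A correlation of 0.5 is what two comparisons with one shared control arm have under 1:1:1 allocation (Trial design {8}), given equal variances. That is moderate dependence, and it should earn only a small relaxation of the Bonferroni level of 0.025. A move up to 0.035 looks too generous.

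At stake are the stated type I error for the two primary hypotheses, the joint coverage of the intervals and the stated power.

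**Working it through.** **Inputs.** From Sample size {14}: overall alpha 0.05, two comparisons, correlation r = 0.5, per-test alpha 0.035, effect size d = 0.5, 90% power, 92 per group, 20% attrition. From section {20a}: two-sided tests and 96.5% intervals.

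**1. The plan's own sample size.** The critical value for two-sided 0.035 is z = 2.108.

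- n per group = 2(2.108 + 1.2816)² / 0.5² = 8 × 3.390² = 91.9, so 92.
- Power at 92 per group is 90.0%.
- 3 × 92 = 276, and 276 / 0.8 = 345.

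The stated figures reproduce. The sample size arithmetic is right, given 0.035.

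**2. Family-wise error at 0.035.** Under the null for both comparisons, the test statistics (Z₁, Z₂) are approximately bivariate normal with correlation r, and

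FWER = 1 − P(|Z₁| < 2.108 and |Z₂| < 2.108).

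| r | FWER at 0.035 per test |
|---|---|
| 0 | 6.9% |
| 0.4 | 6.6% |
| 0.5 (the plan's value) | 6.4% |
| 0.6 | 6.2% |
| 0.7 | 5.9% |
| 0.8 | 5.6% |
| 0.90 | 5.0% |

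At r = 0.5 the unrounded value is 0.0644, so the joint coverage of the two 96.5% intervals is 93.6%. Reading 0.035 as a one-sided level does not help: the error is then 6.3%.

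**3. The level that gives 5%.** Solving FWER = 0.05 at r = 0.5 (Dunnett's method for two comparisons, large sample) gives a per-test alpha of 0.02696, with critical value 2.212. The matching intervals are 97.3%. The ratio 2.212 / 2.108 = 1.049, so the planned intervals are about 5% too narrow.

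**4. Where 0.035 may come from.** This is an inference, since the article names no method. Two shortcuts come close: 0.05 / 2^0.5 = 0.0354 and 1 − 0.95^(1/2^0.5) = 0.0356. Both shrink the number of tests from 2 to 2^(1−r). Neither holds 5% at r = 0.5, as step 2 shows. The finding does not depend on which was used.

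**5. Effect on power.** The non-centrality is 0.5 × √(92/2) = 3.391.

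- At 0.027: power = Φ(3.391 − 2.212) = 88.1% (87.6% with the t distribution).
- To keep 90% at 0.027: n = 8(2.212 + 1.2816)² = 97.6, so 98 per group, 294 in total, and 294 / 0.8 = 367.5, about 368 recruited.

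**The case against.** The strongest counter-arguments concern weight and remedy, not the arithmetic.

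- **The excess is small.** It is 1.4 percentage points, and it decides the outcome only if a p value falls between 0.027 and 0.035. Two unadjusted tests at 0.05 would give 9.1%, so the plan does most of the work. This is fair on size. It does not make the 5% statement true.
- **0.027 is not exact for the planned model.** The mixed model in section {20a} has therapist random effects in the active arms only, so the correlation may differ from 0.5. At r = 0.3, 0.027 gives 5.2%. This stands as a caveat, but 0.5 is the plan's own value and the deviation is much smaller than the present one. Bonferroni at 0.025 would avoid the assumption.
- **88% describes a simple two-mean comparison.** With baseline adjustment, and assuming a baseline–outcome correlation of 0.3 to 0.5 (not given in the article), power at 0.027 would be about 91% to 96%. With an assumed therapist design effect of 1.1 to 1.2 in the active arm and no baseline adjustment, it would be about 86% to 85%. This is true, but the stated 90% comes from the same simple formula, so 88% is the like-for-like replacement.
- **Correcting alpha does not cover two time points.** The primary outcome is assessed at 16 and 28 weeks. If success at either time counted, four tests at 0.027 would give about 8% to 9%, assuming correlations between times of 0.4 to 0.8. That is a separate question. The plan defines its family as two comparisons, and 0.035 fails even for those.

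**Conclusion.** The concern holds. At the stated correlation of 0.5, two two-sided tests at 0.035 give a family-wise error of 6.4% instead of 5%, about 29% higher in relative terms (6.44 / 5.00 = 1.29). The level that matches the claim is 0.027.

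The result rests on the plan's own correlation and its own family of two tests, with a large-sample normal approximation. It is not sensitive to the correlation: the error stays above 5% for any value below about 0.90. The size is moderate and the sample size calculation is otherwise sound. It still needs correcting, because the stated alpha, correlation and overall level cannot all be true, and they set the decision rule for the primary hypotheses.

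**What to change.** - **Sample size {14}:** replace 0.035 with 0.027 per test and name the method (Dunnett, two comparisons with a shared control, r = 0.5). State that 92 analysed per arm gives 88% power at d = 0.5. Keep 345 as the recruitment target.
- **Statistical methods {20a}:** replace 96.5% with 97.3% intervals for the two primary comparisons with TAU, and judge their two-sided p values against 0.027.
- **Scope:** say that 0.027 covers one test per therapy arm, so that it is not read as also covering the two time points.

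If the trial team prefers not to rely on the correlation, Bonferroni at 0.025 with 97.5% intervals is a valid alternative, with 87.5% power by the same formula. If 0.035 is kept, the claim of 5% overall has to be withdrawn and 6.4% stated.

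The cost is wording in two sections and a stated power about 2 points lower. No participants are added. The change should be made before unblinded results are seen, since a later change of threshold would look driven by the data.

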### Recruitment {15}

Participants will be recruited from NHS mental health services linked to each of the four university trial sites (at least 2 NHS settings per site) with identical procedures followed at each. Participants will be identified through close liaison with clinical staff. After clinical staff have confirmed that a potential participant is suitable to be approached (i.e. meets study criteria and no clinical contra-indications), research workers will meet each potential participant to discuss the study, provide written information and time to consider it, respond to questions and seek written informed consent.

We also intend to use recruitment databases or consent for contact initiatives where available to maximise the pool of potential participants. Finally, we can be approached directly by service users interested in taking part and intend to place recruitment posters in the main clinical areas of specialist mental health teams, as well as promoting the trial through online platforms (Twitter, trial website) to facilitate this. In all such instances, we will contact the relevant clinical team and discuss suitability for participation.

## Assignment of interventions: allocation

### Sequence generation {16a}

A randomisation list will be prepared independently by the King’s Clinical Trials Unit using random permuted blocks, stratified by site and baseline voice characterisation An allocation sequence (1:1:1) will be generated, using random permuted blocks of varying size, and stratified by site (4 sites) and baseline voice characterisation (more/less) as defined by meeting the threshold for more highly characterised voice on the characterisation checklist.

### Concealment mechanism {16b}

The allocation sequence will be held independently of the research team and each participant’s allocation revealed via a secure web-based service hosted by King’s Clinical Trials Unit.

### Implementation {16c}

Once a participant has completed baseline assessments, the site trial coordinator will perform the randomisation utilising the web-based service and inform the participant.

## Assignment of interventions: blinding

### Who will be blinded {17a}

Trial coordinators who will not be blind to individual allocations to allow them to inform participants of assignment. The research workers who conduct assessments will remain blinded to the allocation of participants until after the participant has completed their involvement in the trial. These research workers will not be exposed to therapy records whilst they remain blinded. We will be using a system of web-based data entry that ensures assessors do not have access to information in the database that might reveal allocation. Participants will be reminded not to discuss their allocation with research workers when they meet them for the assessment. The senior trial statistician will be blind throughout the study; the trial statistician will be unblind at a group level after the first DMEC meeting. The Statistical Analysis Plan will be prepared before any unblinding of the trial statistician, and only amended by the senior trial statistician.

### Procedure for unblinding if needed {17b}

There are no pre-determined situations in which blinded research workers should become unblinded. Breaks in blindness will be monitored and recorded and where operationally feasible assessments will be allocated to another (blinded) research worker.

## Data collection and management

### Plans for assessment and collection of outcomes {18a}

Assessments will be completed at baseline, after treatment at 16 weeks, and at 28-week follow-up. Participants who have consented will also complete an additional ESM assessment at each time point, responding to questionnaires administered through a smartphone 10 times a day for 6 days. This will be delivered using an application (M-Path, https://m-path.io/landing/) which can be downloaded to the participant’s own phone. Where the participant does not have a smartphone or has concerns about using their own, a smartphone will be provided to them. At the end of the 6 days, the research worker will meet the participant again to complete a debrief questionnaire regarding their experiences of the ESM and to collect the smartphone where this has been provided.

All these assessments will be administered by trained local research workers, who will be supervised by experienced research clinical psychologists. Assessments will be conducted at locations convenient for the participant (at either NHS, University or residential locations).

#### COVID-19

All assessments will take place remotely via a video-conferencing application or telephone, in line with NHS trust and University guidance. Questionnaires should be completed online where possible; that is, where the person has a laptop/tablet and a Wi-Fi connection. Where this is not possible, they will be posted with a stamped addressed envelope to be returned. In the event of social distancing restrictions, additional measures will be taken to manage any distress that occurs with the research team liaising closely with the clinical team caring for the person. The content of the assessment will be as described below.

A sub-sample of participants, approximately 20, who give their consent, will be consecutively recruited across all sites and from both therapy arms in the study to take part in a qualitative interview. This will occur in the final year of the trial, and once those approached have concluded their participation in all assessments in the trial. This interview and the conduct of this sub-study will be developed in collaboration with service user consultant researchers, working with the research team, and will ask participants for feedback on how they found the therapy, taking part in the trial and the technology/software involved.

### Plans to promote participant retention and complete follow-up {18b}

Research workers will maximise engagement with participants and facilitate their completion of follow-up assessments. This includes flexibility around the locations of assessments (home visits where risk assessment is completed) and covering travel expenses for participants. As all outcome measures are through interviews or self-report measures these cannot be completed with participants who discontinue their participation.

### Data management {19}

All data are anonymised at source. No patient identifiable information is recorded on the research assessment records and the computerised database is held centrally and managed by the King’s Clinical Trials Unit. A web-based electronic data capture (EDC) system will be designed, using the InferMed Macro 4 system. The EDC will be created in collaboration with the trial analyst/s and the CI and maintained by the King’s Clinical Trials Unit for the duration of the project. It will be hosted on a dedicated server within KCL. Experience sampling data will be uploaded via a secure network to a Research Electronic Data Capture (REDCap) database managed by the University of Leuven, Belgium who will be conducting the ESM data analysis.

Source data will be entered by recruiting site staff, typically within 7 days of data collection by authorised staff onto the EDC. A full audit trial of data entry and any subsequent changes to entered data will be automatically dated and time-stamped, alongside information about the user making the entry/changes within the system. Database access will be strictly restricted through user-specific passwords to the authorised research team members.

The CI team will undertake appropriate reviews of the entered data, in consultation with the project analyst for the purpose of data cleaning and will request amendments as required. No data will be amended independently of the study site responsible for entering the data*.* In order to ensure the accuracy of the data entered into the database, the primary outcome measure entry will be checked for every participant by comparing the paper record with that on the database. An error rate of no more than 5% is acceptable. This will be completed once all possible assessments for each time point have been completed. If the error rate is higher than 5%, advice will be sought from the trial statisticians regarding further data checking. At the end of the trial, there will be a central process of data cleaning and checking to verify that all the data are complete and correct. At this point, all data will be formally locked for analysis.

Audio recording equipment will be used to record assessments to check fidelity to assessment protocols and to ensure interrater reliability of the PSYRATS-AH (primary outcome) and the Voice Characterisation Checklist (stratification tool). The therapy sessions will be audio recorded (with participant consent) for monitoring the intervention in terms of fidelity and competence. These audio files named with a unique participant identifier will be stored as computer files on secure NHS/ University servers.

All personal data will be kept in a locked filing cabinet in a locked office at the four trial sites and will be accessible only by researchers. Therapy files will be kept in a secure office and are not accessible to the staff collecting the research outcome data. Audio recordings of the therapy will be stored as described above, accessible to the patient's trial therapist and to the senior research clinician supervising that therapist.

